### Process evaluation and cost-effectiveness

To determine the feasibility of the intervention and to identify factors that may influence its effectiveness, a process evaluation will be conducted. The Medical Research Council (MRC) guidelines for process evaluation of complex interventions [77] will be used to examine implementation (e.g. dose, fidelity), mechanisms of impact, and effect of context on implementation and outcomes. Process data will be gathered via analyses of documents, and qualitative interviews with trainers and study participants. Assuming that the intervention will be effective, a cost-effectiveness analysis will be performed from both a healthcare and societal perspective [78].

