### Statistical analysis

#### Sample size calculations

Sample size calculations are based on the primary outcome measures (stress, smoking, and perceived health). To the best of our knowledge, no previous studies have evaluated a similar intervention in low-SES groups. Therefore, it is challenging to determine a prior the necessary sample size for multicomponent behavioral interventions. Previous studies that have evaluated similar components on other outcome measures recommend to aim for a sample size of 20-500 participants per intervention condition with an alpha error of 0.05 and a power of 0.80. to detect the expected effect. Assuming expected attrition of 10%, an initial sample of 300 participants are needed, thus 150 in each intervention condition. All power calculations are done using G*Power [76].

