## Discussion

This paper describes the protocol for an RCT designed to evaluate the effectiveness of a multicomponent theory-based intervention. It is hypothesized that after a successful implementation of the intervention, the intervention will lead to a reduction in stress, smoking, and improvement in financial and self-perceived health. Previous studies have raised concern about the lack of effective interventions for low-SES populations [16]. By conducting this study, we hope to fill these evidence gaps. This study has several strengths. A key strength is the originality of the study. To the best of our knowledge no previous studies have evaluated the effects of similar components used in the current study to reduce stress, smoking, improve financial and self-perceived health in low-SES groups. Another strength of the current study is that it addresses the efficacy of the intervention by using an RCT design. Random allocation of study participants to the different conditions excludes all possible bias (selection and allocation bias). Another strength is the follow-up period of 12 weeks which allows insight into short-term effects. Finally, by incorporating a process evaluation and a cost-effectiveness analysis, we can gain insight into the facilitators/barriers of the implementation and whether the intervention can be scaled up in different settings, respectively. Finally, the intervention will be conducted in a real-life setting, which will make to generalize the effects to similar low-SES groups in the Netherlands.

Some limitations should be considered. First nonadherence and drop-outs could occur. Previous studies have indicated that low-SES individuals drop out quickly from preventive interventions [17]. In the current study, we have taken this into account. In order to prevent high dropout and maintain participation retention, we have used nudges, to reward and motivate the study participants to stay engaged in the intervention. In addition, the use of buddies for the financial support can be a risk for professionalism of our interventions because these buddies are unexperienced. However, the risk is minimal because these buddies are selected carefully and receive extensive training on financial debts by trained psychologists. By using trained buddies, the intervention costs will be very low. If proven effective, the intervention can be scaled up to different settings which could be an advantage for its cost-effectivity.

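### The cost-effectiveness analysis depends on the intervention being effective, yet the Discussion counts on it without condition to answer the scale-up question

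*Protocol article*

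**What the plan says.** The Methods section on process evaluation and cost-effectiveness plans two additional pieces of work. The process evaluation is planned outright. The economic analysis carries a condition: "Assuming that the intervention will be effective, a cost-effectiveness analysis will be performed from both a healthcare and societal perspective". The article plans no economic analysis for the case where effectiveness is not shown.

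The Discussion lists both pieces as a strength, with no condition: "by incorporating a process evaluation and a cost-effectiveness analysis, we can gain insight into the facilitators/barriers of the implementation" and, as the matching contribution of the cost-effectiveness analysis, "whether the intervention can be scaled up in different settings, respectively". Later in the same section it links scale-up to a proven effect: "If proven effective, the intervention can be scaled up to different settings which could be an advantage for its cost-effectivity". It also expects the programme to be cheap, because the support is given by trained buddies.

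The sample size section gives the only error rates in the article: "with an alpha error of 0.05 and a power of 0.80".

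**The concern.** An effectiveness test and a cost-effectiveness analysis answer different questions. The first asks whether the effect can be told apart from zero. The second sets the estimated effect against the estimated cost, with the uncertainty in both. A result that misses significance can still leave room for a worthwhile benefit. When the programme is expected to be cheap, as here, a small or imprecise effect may still be worth paying for. That is a case in which the plan, as written, would produce no economic result.

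Two things are at stake. First, the Discussion gives the scale-up question to an analysis that may not be done. Second, whether an economic result is available would depend on which way the effect result went, which is reporting that depends on the outcome. Across trials run this way, the economic results that exist would come from the more favourable effect estimates.

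**Working it through.** **The plan's own figures.** The article gives no cost-effectiveness figure to reproduce. Its sample size statement is "Assuming expected attrition of 10%, an initial sample of 300 participants are needed, thus 150 in each intervention condition". Only the attrition step can be checked: 270 / (1 − 0.10) = 300 and 135 / (1 − 0.10) = 150. The effect size behind it is not stated. Solving backwards for two equal groups of 135, two-sided 5% and no clustering, 80% power corresponds to d = (1.960 + 0.842) × √(2/135) = 0.34. Actual power is therefore unknown, and 80% is the planned value only.

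**The statements side by side.**
- Methods: economic analysis if the intervention is effective; process evaluation in any case.
- Discussion, strengths: both are incorporated, and the economic analysis informs scale-up. No condition.
- Discussion, later: scale-up follows if effectiveness is proven.

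The first and third agree with each other. The second promises more than the first delivers.

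**Illustration of size.** Assumptions, none of them in the document: one normally distributed effect estimate; the analysis is run only if z > 1.96 in favour of the intervention; the same outcome is the economic effect measure; incremental cost is fixed.

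Let δ = 1.960 + z(power) be the true effect in standard errors. Then

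E[Z | Z > 1.96] / δ = 1 + φ(1.960 − δ) / (power × δ).

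- 80% power: δ = 2.802; φ(−0.842) = 0.280; 0.280 / 0.80 = 0.350; 1 + 0.350 / 2.802 = 1.125. No analysis in 1 − 0.80 = 20% of trials.
- 70% power: δ = 2.484; φ(−0.524) = 0.348; 0.348 / 0.70 = 0.497; 1 + 0.497 / 2.484 = 1.20. No analysis in 30%.
- 50% power: δ = 1.960; φ(0) = 0.399; 0.399 / 0.50 = 0.798; 1 + 0.798 / 1.960 = 1.41. No analysis in 50%.

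A simulation of 2,000,000 draws at 80% power gave the cost per unit of effect, relative to its true value and among significant trials only, as 0.92 at the median and 0.94 at the mean. Cost divided by the mean effect is 1 / 1.125 = 0.89. The size thus depends on the scale used.

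**Why these sizes cannot be carried over to this trial.** The article has several primary outcomes and two active arms, and it does not say which result counts as effective. Take the three outcomes in the abstract and suppose, for simplicity, that they are independent with 80% power each. If any one success were enough, the chance of no analysis would be 0.20³ = 0.8%. If all three were required, it would be 1 − 0.80³ = 49%. If the economic effect measure differs from the outcome that decides, the 0.35 standard error excess at 80% power shrinks in proportion to their correlation.

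**What the fix changes in a single trial.** If the trial is positive, the analysis is run with or without the condition, on the same data, and gives the same estimate. The only difference arises when the trial is not positive: an analysis then exists that otherwise would not.

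**The case against.** The strongest case on the other side has four parts.

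1. The wording may express the authors' expectation and not a rule, and it names no test or threshold. This stands in part. A formal significance threshold is not in the text and is only assumed in the illustration. The natural reading is still conditional, and the later Discussion sentence on proven effectiveness supports it. If no condition was meant, the same edit removes the doubt.

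2. A reader might infer that the condition biases this trial's cost per unit of effect downward by 12% or more. The documents do not support that. In a positive trial the estimate is the same either way, and the inflation given significance affects the trial's own effectiveness estimate equally. The percentages describe which results become available over repeated trials, not an error that deleting the condition would correct.

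3. On the authors' own logic, scale-up arises only once effectiveness is proven, so Methods and Discussion may be consistent in intent. This softens the mismatch to a missing caveat in the strengths sentence. It does not answer the main point, because failing to prove an effect does not show that the programme is poor value.

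4. Staging the economic work after a positive result is a choice about resources, and an article may leave the definition of effective to a fuller document. Both are fair. The missing definition is not counted as a fault here. A reader might also infer that no cost data would be collected or reported after a null result, but the article does not say so.

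**Conclusion.** The point holds as a minor one that is cheap to correct. The Methods section makes the economic analysis depend on effectiveness, and the Discussion relies on it without that condition. A missed effect test does not settle cost-effectiveness, so the plan as written can leave its own scale-up question unanswered.

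The size is not fixed by the document. Under the single-outcome illustration at 80% power, one in five trials of a truly effective programme would give no economic analysis, and the effects behind the published ones would average about 12% too large. Both figures rest on the assumptions listed above and on power that the article states but that cannot be verified from it. They should not be quoted as a bias in this trial's estimate.

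**What to change.** Delete the opening condition in the section on process evaluation and cost-effectiveness. Replace the sentence with wording such as: *A cost-effectiveness analysis will be performed from a healthcare and a societal perspective whatever the results on the primary outcomes. It will use the randomised comparison and report the joint uncertainty of incremental cost and effect.* The strengths sentence in the Discussion then agrees with the Methods and needs no caveat.

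The cost is one sentence now, and extra analysis work later only if the trial is not positive. The edit makes the economic result available in every case. It does not alter the estimate after a positive result.

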## Discussion

This paper describes the protocol for an RCT designed to evaluate the effectiveness of a multicomponent theory-based intervention. It is hypothesized that after a successful implementation of the intervention, the intervention will lead to a reduction in stress, smoking, and improvement in financial and self-perceived health. Previous studies have raised concern about the lack of effective interventions for low-SES populations [16]. By conducting this study, we hope to fill these evidence gaps. This study has several strengths. A key strength is the originality of the study. To the best of our knowledge no previous studies have evaluated the effects of similar components used in the current study to reduce stress, smoking, improve financial and self-perceived health in low-SES groups. Another strength of the current study is that it addresses the efficacy of the intervention by using an RCT design. Random allocation of study participants to the different conditions excludes all possible bias (selection and allocation bias). Another strength is the follow-up period of 12 weeks which allows insight into short-term effects. Finally, by incorporating a process evaluation and a cost-effectiveness analysis, we can gain insight into the facilitators/barriers of the implementation and whether the intervention can be scaled up in different settings, respectively. Finally, the intervention will be conducted in a real-life setting, which will make to generalize the effects to similar low-SES groups in the Netherlands.

Some limitations should be considered. First nonadherence and drop-outs could occur. Previous studies have indicated that low-SES individuals drop out quickly from preventive interventions [17]. In the current study, we have taken this into account. In order to prevent high dropout and maintain participation retention, we have used nudges, to reward and motivate the study participants to stay engaged in the intervention. In addition, the use of buddies for the financial support can be a risk for professionalism of our interventions because these buddies are unexperienced. However, the risk is minimal because these buddies are selected carefully and receive extensive training on financial debts by trained psychologists. By using trained buddies, the intervention costs will be very low. If proven effective, the intervention can be scaled up to different settings which could be an advantage for its cost-effectivity.

In summary, this study will add to the existing knowledge in that we: 1) focus on improving the health of low-SES individuals by targeting multiple factors; 2) use a theory-based multicomponent intervention instead of a single-component intervention; and 3) conduct the study in a real-life setting among a vulnerable population. Taken together, the findings of the current study will contribute to filling the evidence gaps. If proven effective, the findings from the present study will serve to inform future directions of research and clinical practice with regard to behavioral change interventions for low-SES populations on a national and international level.

### Trial status

The BeHealthyR study is currently ongoing. Data collection will be completed in June 2019.

## Abbreviations

BCI: Behavioral change intervention
BCT: Behavioral change techniques
CBSM: Cognitive behavior stress management
CBT: Cognitive behavior therapy
CC: Control condition
CM3: Cardio and Motion Monitoring Module
CO: Carbon monoxide
COHb: Carboxyhemoglobin
CSI-SF: Coping Strategies Inventory Short Form
DASS-21: Depression Anxiety Stress Scale
DMSC: Data Monitoring Steering Committee
EUC: Erasmus University College
EUR: Erasmus University Rotterdam
FTND: Fagerstrom Test for Nicotine Dependence
GATS: Global Adult Tobacco Survey
GDPR: General Data Protection Regulation
HRV: Heart rate variability
MRC: The Medical Research Council
N/A: Not Applicable
PP: Positive psychology
PPG: Photoplethysmographic
PSWQ: Penn State Worry Questionnaire
RCT: Randomized controlled trial
RSQ: Responses to Stress Questionnaire
SCT: Social cognitive theory
SES: Social economic status
SF: Short Form
SM: Stress management condition
SM-B: Stress management with a buddy condition
SPIRIT: Standard Protocol Items Recommendations for Intervention Trials
TMSC: Transactional model of stress and coping
WVS: World Values Survey
